### Recruitment

Participants will primarily be recruited via the Alberta Cancer Registry (Alberta Health Services, Canada). Data extraction criteria include age (≥ 18 and ≤ 75 years), diagnosed with any invasive cancer from 2013 to 2016, and postal codes within 20 km of the University of Calgary. From the resulting extraction, equal numbers of males and females will be randomly sampled and sent a letter confidentially and anonymously via the Registry. Those contacted will be under no obligation to respond to the research team. Participants will also be recruited via liaising with clinicians and/or advertising at cancer centres local to the University of Calgary. When interested participants contact the study co-ordinator (via phone or email), they will be informed about the main aspects of the research and asked about the time since their last cancer treatment, and fatigue severity. If potentially eligible, participants will be provided with the participant information sheet and encouraged to ask questions about the risks and benefits of participation. Once the participant has had time to review the information, the first visit to the laboratory (Lab Visit #1) will be scheduled.

### Randomization

Due to a continuous enrolment strategy and relatively small sample size, participants will be allocated to groups using a dynamic allocation procedure (minimization, performed using an open-source, online minimization program (MinimPy Program 0.3) [68]. In this process, the first participant is allocated randomly to one of two treatment groups. Each newly enrolled participant is hypothetically allocated to each treatment group and an imbalance score is calculated given unweighted baseline categorical variables: sex (male, female), age group (18–39, 40–49, 50–59, 60–75) and cancer type (breast, prostate, lung, colorectal, other). The participant will be allocated to the preferred group (least imbalance) with a 1:1 allocation ratio, and a randomisation weighting of 0.75 in order to avoid the potential introduction of bias associated with pure minimization [69]. Participants will be randomized following completion of all baseline assessments (i.e. after Lab Visit #2, see below), by a researcher who is independent of the recruitment, enrolment and laboratory assessment process, and who has password-protected access to the allocation procedure for the trial within the online minimization program.

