A number of behavioural interventions have been investigated for the improvement of CRF in adults (e.g. [28]), but there is widespread agreement the most beneficial intervention is exercise ([29–31]). However, a systematic review of several meta-analyses recently highlighted that although effects are in the direction of benefit, the magnitude of the effect of exercise on CRF varies substantially, such that caution is warranted when drawing definitive conclusions about exercise and CRF [32]. CRF is often a secondary rather than primary outcome of randomized controlled trials, and participant level of CRF at baseline is not necessarily clinically relevant, meaning that the effect of exercise on CRF may actually be diluted [32]. In addition, exercise interventions may not be optimally designed with an improvement in CRF as the target. Nevertheless, due to numerous health benefits, exercise should be part of standard care for cancer survivors, and the American College of Sports Medicine (ACSM) has published specific recommendations for exercise and CRF [33]. In accordance with other published guidelines [34–37], a combination of aerobic and resistance training is recommended, and the health-related physical activity guidelines for the general population are considered appropriate for most cancer survivors (with modifications as necessary for cancer-related side effects). However, it has also been suggested that this ‘one size fits all’ approach may be too generic, particularly in regards to the treatment of persisting side effects such as CRF [38].

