### Study population

The majority of research in exercise and cancer has been conducted in female breast cancer survivors due to high prevalence and survival estimates [10]. However, CRF is not unique to a specific tumour group or cancer-treatment type. Furthermore, demographic and clinical characteristics do not moderate exercise-induced improvements in other patient-reported outcomes such as physical function and HRQL [64]. Our intention is to offer this program as widely as possible to a heterogeneous group of cancer survivors who are experiencing CRF after treatment. Therefore, male and female cancer survivors aged 18–75, following any cancer diagnosis and cancer-treatment type, will be recruited for the study. Potential participants will be screened for study inclusion using a score of CRF severity using the FACIT-F questionnaire [4] (where a score of ≤34 is the recommended cut-off point for the diagnosis of CRF [65]). Additional inclusion and exclusion criteria are presented in Table 1.

**Table 1 Tab1:** Inclusion and Exclusion Criteria

Inclusion Criteria	Aged ≥ 18 and ≤ 75 years
	FACIT-F score ≤ 34
	Completion of primary treatment in ≥ 3 months and ≤ 5 years from enrolment
	Approval received from CSEP-CEP and/or physician
	Command of the English language and ability to understand instructions related to the study procedures
Exclusion Criteria	Contraindication to experimental procedures and/or exercise
	Previously diagnosed as having sleep apnea or anemia
	Currently participating in a structured exercise program or another clinical trial
	Participant is pregnant

*CSEP-CEP* Canadian Society for Exercise Physiology Certified Exercise Physiologist, *FACIT-F* Functional Assessment of Chronic Illness Therapy-Fatigue, *TMS* transcranial magnetic stimulation

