### Sample size

An a priori sample size estimation was performed using G*Power 3 (v3.1.2–3.1.9 [66]). The hypothesis was treated as a time × treatment (within-between) interaction for the primary outcome measure of score on the FACIT-F. A standardized mean difference of 0.44 was used, as reported in a 2012 Cochrane review for comparisons of CRF following an exercise intervention or control, from a total of 539 cancer survivors after anti-cancer therapy [29]. Using an α level of 0.05, a 1 - β of 0.8, the total sample size was calculated as 44. Potential loss to attrition was estimated as 15%, based on previous reports from supervised exercise interventions in cancer survivors post-treatment (e.g. [67]), and thus the total sample size was calculated as 52.

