#### Cancer-related fatigue

Score on the FACIT-F will be used to assess CRF severity (primary outcome). The revised Edmonton Symptom Assessment System (ESAS-r) tiredness scale will also be used [87, 88], as recommended for the screening of CRF severity in the clinical practice guidelines for standard cancer care in Alberta [89]. The questionnaires will be completed between 8:30–9:30 am.

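### Minimisation leaves out baseline FACIT-F, the primary outcome, although it is known before allocation: a minor, cheap improvement that guards against chance imbalance

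*Protocol article*

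**What the plan says.** All references are to the protocol article.

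- **Factors.** Randomization lists them in full: "unweighted baseline categorical variables: sex (male, female), age group (18–39, 40–49, 50–59, 60–75) and cancer type (breast, prostate, lung, colorectal, other". Small sample size is among the reasons given there for minimising.
- **Random element.** Participants go to the preferred arm "with a 1:1 allocation ratio, and a randomisation weighting of 0.75".
- **Timing.** "Participants will be randomized following completion of all baseline assessments (i.e. after Lab Visit #2, see below".
- **Primary outcome.** Under Lab visit #2, Cancer-related fatigue: "Score on the FACIT-F will be used to assess CRF severity (primary outcome". Table 2 places FACIT-F at recruitment and again at Lab Visit #2. Eligibility (Table 1) requires "FACIT-F score ≤ 34".
- **Sizing.** Sample size: "A standardized mean difference of 0.44 was used", giving 44, raised to 52 for 15% attrition.
- **Analysis.** Intended statistical analysis specifies a linear mixed model for FACIT-F over time, with arm as fixed effect and participant as random effect. It names neither baseline FACIT-F nor the minimisation factors as covariates. A difference of at least 3 points counts as clinically relevant.

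**The concern.** A baseline score ordinarily predicts the same score later, so it is a natural candidate for balancing in a small trial. Here it exists before every allocation and needs no new data, yet it is left to chance. If the arms start unequal, the more fatigued arm tends to improve more through regression to the mean, and a comparison of change without baseline adjustment carries part of that into the arm contrast. At stake are the precision and credibility of the primary comparison in an unblinded trial with a self-reported outcome, where a visible baseline gap would be awkward to explain.

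**Working it through.** **1. The plan's own figure.** Take a two-group, two-time-point interaction with f = 0.44/2 = 0.22 and pre–post correlation ρ = 0.5 (assumed; the article gives none). Then λ = N·f²·m/(1−ρ) = 44 × 0.0484 × 2/0.5 = 8.52, and power is 0.814 at N = 44. With attrition, 44/0.85 = 51.8, so 52, or 26 per arm. Both stated figures reproduce.

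**2. Size of a chance gap, in SD units.** The standard error of the baseline arm difference is √(2/26) = 0.277.
- 95% of gaps lie within ±1.96 × 0.277 = ±0.54 SD.
- P(gap > 0.44 SD) = 2[1 − Φ(0.44/0.277)] = 11.3%.

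**3. Check by simulation of the stated scheme.** N = 52, probability 0.75 to the preferred arm, assumed frequencies for sex, age group and cancer type. Runs of 3,000 and 4,000 trials were made under different FACIT-F assumptions.

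| Allocation | SD of baseline gap | P(gap > 0.44 SD) |
|---|---|---|
| As stated | 0.276–0.281 | 11–12% |
| Plus FACIT-F, two levels | 0.204 | 3% |
| Plus FACIT-F, three bands | 0.19–0.20 | 2–3% |

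**4. In points.** The article gives no FACIT-F SD. For assumed SDs of 5, 6, 7, 8, 9 and 10 points, the chance of a baseline gap of at least 3 points at 26 per arm is 3%, 7%, 12%, 18%, 23% and 28%.

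**5. How much of a gap reaches the result.** In an unadjusted pre–post change contrast the carried share is (1−ρ).
- ρ = 0.5: a 0.30 SD gap shifts the contrast by 0.15 SD and a 0.44 SD gap by 0.22 SD.
- For the 0.44 SD gap, the shift is 0.26 SD at ρ = 0.4 and 0.13 SD at ρ = 0.7.

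**6. Gain if the analysis stays unadjusted.** The baseline share of change-score variance is (1−ρ)²/[2(1−ρ)] = (1−ρ)/2, that is 0.30 at ρ = 0.4 and 0.15 at ρ = 0.7. The two-level factor removes 1 − (0.204/0.281)² = 0.47 of it. The variance of the contrast falls by 0.30 × 0.47 = 14% and 0.15 × 0.47 = 7%.

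**7. Gain if baseline is a covariate.** Imbalance D inflates the variance of the adjusted contrast by roughly D²/4. The average inflation is 0.281²/4 = 2.0% as stated and 0.204²/4 = 1.0% with the factor, a gain of about 1%. The fuller estimate is 1–2%.

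**8. Error rate and power (simulated, ρ = 0.5, three bands; simulation error about ±0.004 at the 5% level).**
- Type I error, stated scheme: 0.043 for a change score, 0.050 baseline-adjusted.
- Type I error, factor added: 0.038 and 0.051. Across runs the unadjusted test becomes conservative, at about 0.036–0.043, because its standard error ignores the balancing.
- Power for a 0.44 SD post-intervention difference at N = 52, used only to compare options: 0.34 for a change score under the stated scheme, and 0.42 baseline-adjusted with or without the factor.

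**The case against.** The strongest reply is that three minimisation factors for 52 people is ordinary practice, that nothing in Randomization is wrong or self-contradictory, and that the harm comes from the analysis, not the allocation. A chance gap is equally likely in either direction and is already part of the standard error. Once baseline is a covariate almost nothing is left to gain (steps 7 and 8). The article condenses the model, and an analysis plan that is not shown may contain that covariate. All of this stands, and it is why the point is minor.

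Four stronger readings are tempting and are not supported.
- **That the protocol contradicts its own Background.** The remark there, "participant level of CRF at baseline is not necessarily clinically relevant, meaning that the effect of exercise on CRF may actually be diluted", concerns earlier trials that enrolled people without clinically relevant fatigue. It argues for the eligibility cut-off, which the trial applies. It does not claim a gradient of response among eligible participants.
- **That it balances factors it calls irrelevant.** The statement in Study population, "demographic and clinical characteristics do not moderate exercise-induced improvements in other patient-reported outcomes such as physical function and HRQL", is about effect moderation in other outcomes and justifies broad recruitment. Balancing factors may be chosen for prognosis or face validity, so there is no inconsistency.
- **That every fatigue-related secondary outcome is compromised.** No calculation supports this.
- **That a 0.44 SD gap could cancel or mimic the planned 0.44 effect.** Only the share (1−ρ) passes through, and only without adjustment.

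What the reply does not remove is that the score is available and costs almost nothing to use, and that the analysis as described in the article would not absorb a gap.

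**Conclusion.** The point holds as a minor, cheap improvement. The allocation rule omits the baseline value of the primary outcome although it is in hand, leaving about a 1 in 9 chance of a baseline gap above 0.44 SD, which a two-level factor reduces to about 3%. The design is valid as it stands: this is chance imbalance, with no bias and no inflation of type I error.

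The gap probability for the stated scheme rests on 26 per arm and, in the simulations, on assumed factor frequencies; the re-derivation also took those factors as unrelated to FACIT-F. If they are related, the existing scheme already balances FACIT-F in part. The carry-over and variance figures rest on assumed correlations of 0.4 to 0.7 and a two-time-point change contrast; the figures in points rest on assumed SDs. Whether a baseline covariate is planned elsewhere cannot be settled from the article.

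**What to change.** Make two changes together.

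1. Add Lab Visit #2 FACIT-F as a two-level minimisation factor, entered by the independent researcher who already runs the allocation. Set the cut-point below 34 in advance. The article gives no FACIT-F distribution, so recruitment-stage scores, viewed without reference to arm, are one source for it.
2. Include baseline FACIT-F as a covariate in the primary model. This gives most of the precision gain and makes the standard error reflect the balancing. The first change without the second leaves the unadjusted test conservative.

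The cost is one extra field, a short amendment through the ethics board, and slightly looser balance elsewhere: in simulation the summed imbalance rises from 5.7 to 6.1 participants for age group and from 6.6 to 7.2 for cancer type. The sample size stays at 52. The allocation change helps only participants not yet allocated; if enrolment is well advanced, the covariate alone is worth adding.

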### Blinding

During the assessments before the intervention, the participants and study team will be blinded to group assignment as this occurs before randomization. Following randomization, blinding of participants and the study team is not possible due to the recognised complexity of blinding to an exercise intervention [29], particularly in the case of interventions that are tailored to the individual, and where the study team will communicate about participant wellbeing. Data files will be anonymized using a code by an independent researcher who is unrelated to the study prior to processing by study personnel. Participants will be informed that there is equal possibility that they will be assigned to one of the two treatment groups, and that the relative impact of two exercise interventions is under investigation.

### Laboratory assessments

The study team and/or assessors for specific methods are extensively trained in those methods, and a number of pilot assessments were performed prior to the study. Regular internal inspections of the methods described below are carried out to maintain high methodological quality. Participants will be required to attend an exercise physiology laboratory (Faculty of Kinesiology, University of Calgary, Alberta, Canada) on four occasions. Lab Visits #1 and #2 take place before the 12-week exercise intervention, and Lab Visits #3 and #4 take place after the intervention. All laboratory visits will commence between 8 am and 9 am and will last 2.5–3 h. Participants will be advised to consume breakfast 1.5 h prior to arrival at the laboratory. Participants will be instructed to arrive to the laboratory hydrated and to refrain from alcohol, caffeine and strenuous activity for the preceding 24 h. Overall study time points are presented in Table 2.

**Table 2 Tab2:** Study Time Points

Process, Outcome or Test	Time Point									
	Recruitment	Pre-Intervention		Intervention			Post-Intervention		Follow-Up	
		Lab Visit		Week (Total = 12)			Lab Visit		Month	
		#1	#2	3	6	9	#3	#4	6	12
Informed Consent		×^a^								
PAR-Q+		×^a^								
ECG		×^a^								
Blood Pressure		×^a^					×			
Resting HR		×^a^					×			
Participant Information		×								
FACIT-F	×		×	×	×	×		×	×	×
ERAS-r			×	×	×	×		×	×	×
FACT-G			×					×		
CES-D		×			×		×	×		
BPI-sf		×			×		×			
SPS		×					×			
GLTEQ		×					×		×	×
ISI		×					×			
Venous Blood Sample		×					×			
Body Mass		×	×				×	×		
Stature		×					×			
Neuromuscular Familiarization		×								
Start of 15-day Actigraphy		×						×		
Sleep Diary		×						×		
HRV			×					×		
Maximal Exercise Test		×					×			
DXA			×					×		
CSA			×					×		
Grip Strength			×					×		
Neuromuscular Function			×					×		
Intermittent Cycling Test			×					×		

^a^Indicates that the item is part of the screening process. BPI-sf, Brief Pain Inventory Short Form, CES-D, Center for Epidemiological Studies on Depression Scale; CSA, cross-sectional area; DXA, dual-energy X-ray absorptiometry; ECG, electrocardiogram; ESAS-r, Edmonton Symptom Assessment System (revised version); FACIT-F, Functional Assessment of Chronic Illness Therapy Fatigue Scale; Functional Assessment of Cancer Therapy - General (FACT-G); GLTEQ, Godin Leisure-Time Exercise Questionnaire; HR, heart rate; HRV, heart rate variability; ISI, insomnia severity index; PAR-Q+, Physical Activity Readiness Questionnaire for Everyone; SPS, Social Provision Scale

### Lab visit #1

#### Informed consent

Following initial communication about the main aspects of the research during the recruitment process, Lab Visit #1 will begin with an in-person discussion with the study coordinator (20–30 min). The participant will have the opportunity to express any concerns and/or ask questions. The participant information sheet will be reviewed and/or explained such that the information is comprehensible, and the study coordinator will seek verbal assurance that the participant understands the research, and that their participation is entirely voluntary. The study co-ordinator will then obtain written informed consent to participate.

#### Screening and participant information

Participants will complete a Physical Activity Readiness Questionnaire for Everyone (PAR-Q+) and will be screened for contraindications to TMS [70]. Participants will be also screened for arrhythmia and hypertension, determined during resting electrocardiography and blood pressure measurements, respectively. Continuation with the study is conditional on the screening process, and physician approval may be sought at this stage. If the participant displays a normal sinus rhythm and systolic and diastolic blood pressure of ≤144 and ≤ 94 mmHg, respectively, is cleared for physical activity by a Canadian Society for Exercise Physiology Certified Exercise Physiologist (CSEP-CEP), and no further concerns are raised that would warrant physician approval, the participant will continue to the procedures described for below. Demographics will be self-identified using a participant questionnaire, and will include sex, age, race, marital status, education, employment status and household income. Clinical variables will include cancer diagnosis, time since diagnosis, time since completion of primary treatment, treatment type (e.g. surgery, radiation therapy, hormone therapy and/or chemotherapy) and persisting side effects. Participants will self-identify as non-smokers or smokers (daily or occasional). The Alcohol Use Disorders Identification Test (AUDIT) will be used as an indication of hazardous and harmful alcohol use (score > 8) [71].

#### Participant-reported outcomes

In addition to CRF severity (Lab Visit #2), patient-reported outcomes include HRQL, depressive symptomatology, pain, social provisions, leisure-time exercise and insomnia severity. The following questionnaires will be completed in the order described and were chosen for their established reliability and validity with specific emphasis on use in cancer populations. HRQL will be assessed using the Functional Assessment of Cancer Therapy – General (FACT-G) [72], which provides scores for subscales of physical well-being, social/family well-being, emotional well-being, functional well-being, and additional concerns specific to cancer type. In addition, the sum of these subscale scores will be used to calculate total score for HRQL. Depressive symptomatology will be assessed using the 20-item Center for Epidemiological Studies on Depression Scale (CES-D) [73]. Pain will be evaluated using the Brief Pain Inventory Short Form (BPI-sf) [74] which measures both pain severity and the impact of pain on functioning (interference). Social provisions will be assessed using the Social Provision Scale (SPS) [75], which provides scores for six sub-groups: guidance, reliable alliance, reassurance of worth, attachment, social integration, and opportunity for nurturance. A total SPS score will be derived from the six sub-scales. Leisure-time exercise will be assessed using a modified Godin Leisure-Time Exercise Questionnaire (GLTEQ) [76], including the frequency and duration of mild, moderate, strenuous, resistance and flexibility exercise.

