### Intended statistical analysis

Data will be analysed after data collection is complete, and no interim statistical analysis will be performed. Descriptive statistics will be used for demographic and clinical variables measured at baseline for each group. Frequencies and percentages will be used for categorical variables and the mean ± standard deviation (or median and range) will be used for continuous variables. To account for any differences in loss to follow up between groups, the primary analysis will be conducted on an intention-to-treat basis. For the primary outcome of FACIT-F score between treatment arms over time, data will be analysed with linear mixed models using R [123] and lme4 [124]. “Treatment arm” will be included as a fixed effect and “participant” as a random effect. Parameters will be estimated using restricted maximal likelihood. The Kenward-Roger approximation for degrees of freedom will be used when evaluating the significance of effects. This produces optimal type I error rates (neither anti-conservative nor overly sensitive to sample size) [125]. Secondary analyses will be performed to assess adjustments for protocol deviations (per protocol analysis). Statistical code will be made openly available upon publication of the results. A minimum of a 3-point difference in FACIT-F score will be considered clinically relevant [126]. For secondary outcomes that are assessed pre- and post-intervention only (e.g. neuromuscular measures, sleep parameters, blood biomarkers), two-way mixed design ANOVA will be used (group [tailored vs. traditional] × time [pre- vs. post-intervention]). In this case, missing data will be dealt with using list-wise deletion. Following a significant interaction, pairwise comparisons will be conducted with a Bonferroni adjustment. The threshold for rejecting the null hypothesis will be *p* < 0.05. For main and interaction effects, partial eta squared will be computed as an effect size estimate. Effect sizes for pairwise comparisons will be reported as Cohen’s *d* [127, 128]. This will be supplemented with 95% confidence intervals for mean differences. Further exploratory analysis will be labelled as such in later reporting.

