The most important decision about the design of this study also represents the most significant challenge. That is, tailored exercise interventions that are designed based on comprehensive (though not exhaustive) pre-intervention assessments. It is not possible to specify all possible aspects of this tailoring in advance, though a number of categories have been detailed. The basis of the tailored intervention is that it involves consideration of individual profiles. For most cancer survivors, the published guidelines offer a foundation for exercise recommendations, given that exercise is considered as being low risk with large potential for benefits. However, in clinical practice and during treatment, exercise prescription does involve tailoring based on adverse events or as recently highlighted, co-morbidities [38]. We propose that specific tailoring may also be necessary for a diverse group of cancer survivors with persistent CRF after treatment completion. Targeting CRF as a symptom, rather than a tumor group or treatment type, will undoubtedly result in a heterogeneous cohort. Although the primary research question is clearly defined, there are multiple degrees of complexity for later interpretation and reporting of study results. Our solution is to make the (anonymized, de-identified) intervention data openly accessible, with the restriction that participant privacy/confidentiality must be maintained. To our knowledge, this is not common practice in exercise oncology research, but will facilitate replication of the characteristics of individual interventions and allow further exploratory analysis in regards to the interpretation and comparison of intervention data.

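### The quality-of-life total, as defined, adds in a subscale that differs by cancer type, so in this mixed-cancer cohort the pooled score has no common meaning

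*Protocol article*

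**What the plan says.** The rule is in the Protocol article, Lab visit #1, Participant-reported outcomes. HRQL is measured with the FACT-G. The subscales begin with physical and social/family well-being, and the list closes with "emotional well-being, functional well-being, and additional concerns specific to cancer type". The text then states that, in addition to the subscale scores, "the sum of these subscale scores will be used to calculate total score for HRQL".

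Four other places bear on this rule:
- Study population: eligible survivors, "following any cancer diagnosis and cancer-treatment type, will be recruited for the study".
- Randomization: one minimization factor is "cancer type (breast, prostate, lung, colorectal, other"), so the design expects at least five diagnostic groups, one of them a catch-all.
- Table 2: the FACT-G is scheduled once before the intervention (Lab Visit #2) and once after it (Lab Visit #4).
- Intended statistical analysis: for secondary outcomes measured only at those two stages, "two-way mixed design ANOVA will be used", with group and time as factors. Partial eta squared, Cohen's d and confidence intervals for mean differences are to be reported. The section mentions no stratification or rescaling by cancer type.

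The Discussion adds that recruiting on a symptom rather than on a tumour group "will undoubtedly result in a heterogeneous cohort".

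**The concern.** A total score can be pooled across participants only if it is the same sum for each of them. Four of the listed components meet that condition. The fifth does not, because the protocol itself describes it as specific to cancer type. A breast cancer survivor and a prostate cancer survivor with identical scores on the four general subscales need not have the same total, and where their totals differ, the difference comes from questions about different things.

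What is at stake is the interpretation of one secondary patient-reported outcome. If the total is computed as described, a reported mean change in HRQL, its confidence interval and its standardised effect size would each average over different constructs, in proportions set by whichever diagnoses happened to be recruited.

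**Working it through.** The documents give no figure for the HRQL total (no item count, range, standard deviation or target difference), so there is nothing to reproduce. The check sets the passages side by side and follows the scoring rule through the analysis.

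**1. What the sum refers to.** The sentence defining the total directly follows the list of five components and refers back to it without restriction. The same section treats the Social Provision Scale in a parallel way: it lists six components and derives the total from all six. The literal reading, a five-part sum, is therefore also the natural one. No other section limits the total to the four general subscales.

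**2. The score in symbols.** Let G be the sum of the physical, social/family, emotional and functional subscales, and let A_c be the additional-concerns score for a participant with cancer type c. As written:

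T = G + A_c

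G has the same definition for everyone. By the protocol's own description, A_c has different content for different c.

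**3. Change from before to after.** For one participant:

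ΔT = ΔG + ΔA_c

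A constant difference in level between cancer types is present at both visits and drops out of ΔT. The content of ΔA_c does not drop out; it remains a change in something that depends on diagnosis.

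**4. The pooled arm comparison.** Let w_c be the proportion of participants with cancer type c, and suppose that minimization makes w_c the same in both arms. Write D for tailored minus traditional. Then:

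D(mean ΔT) = D(mean ΔG) + Σ_c w_c × D(mean ΔA_c)

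The first term is a difference on one scale. The second is an average of differences on several scales, weighted by the recruited case mix. Equal w_c in the two arms removes confounding by cancer type, but it does not make the second term a single quantity. A trial with the same true effects within each diagnosis and a different case mix would estimate a different value.

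**5. Spread and standardised effects.** Differences between cancer types in the level of A_c add to the between-participant variance of T at each visit. Differences between types in ΔA_c add to the variance of ΔT. Cohen's d divides by a standard deviation, so it inherits this. The amount cannot be computed from the documents.

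**6. What is untouched.** FACIT-F is a separate questionnaire with its own model, and the sample size rests on FACIT-F alone. The four general subscales are also to be scored separately, so G can be formed from data already planned.

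**The case against.** The strongest reply is that this is loose wording and not a scoring decision. The only HRQL instrument named in the text, in Table 2 and in the abbreviations is the general form. No breast, prostate, lung or colorectal module is named or scheduled. The investigators may intend a total over the general subscales and have described the instrument carelessly. That is possible, and it would reduce the point to a correction of wording. It does not remove the point: the article states a rule, the rule as stated does not suit the stated population, and no other section corrects it. This is also not detail left to a fuller document, because the article commits to a definition of the total.

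A second reply is that the harm is small. Most of this stands. Cancer type is a minimization factor, level differences cancel in within-person change, and the four common subscales remain available. One qualification is that minimization treats all remaining diagnoses as one category, so balance within it is not assured.

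A reader might also infer more than the documents support:
- *That the treatment comparison for HRQL is biased.* Nothing shows this; balance on cancer type and the pre/post design both work against it.
- *That totals differ between diagnoses by some number of points, or that some participants have no cancer-specific component.* The documents give no item counts, scoring ranges or list of modules. Only a difference in content is documented.
- *That HRQL ranks above the other patient-reported outcomes.* The section lists it with depressive symptoms, pain, social provisions, leisure-time exercise and insomnia, and does not rank them.
- *That comparison with FACT-G totals from other studies would be invalid.* This depends on the instrument's published scoring, which the article does not set out.

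**Conclusion.** The point holds in a limited form. As written, the HRQL total includes a component whose content varies with diagnosis, in a trial that deliberately mixes diagnoses and pools them in one analysis. The pooled mean, mean difference and effect size for that total therefore lack a common meaning across participants, and the score carries some avoidable variance.

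The conclusion rests on two things: the literal reading of the scoring sentence, and the protocol's own statement that the fifth component is specific to cancer type. It needs no assumption about item numbers or ranges. Its numerical size cannot be derived from the documents. It affects the interpretability of one secondary score, leaves the FACIT-F analysis and sample size alone, and does not show bias between arms. If a total over the four general subscales was intended all along, only the sentence is wrong.

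**What to change.** Replace the scoring sentence so that total HRQL is, for every participant, the sum of the four common subscales: physical, social/family, emotional and functional well-being. State that any score for cancer-type-specific concerns is kept out of this total and, if collected, is reported separately.

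The cost is one sentence, made before the data are analysed. The questionnaires, visit schedule, sample size and ANOVA do not change. Separate reporting of the cancer-specific score should stay modest: the planned 52 participants over five cancer-type categories average 52 / 5 = 10.4 per category before attrition, or about 5 per arm, so it would be descriptive at most.
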